## Methods

### Study design

This study is a clinical single-center, prospective, superiority, parallel-group, randomized controlled trial in patients with THS. The study will be conducted at the Department of Treatment Center for Traumatic Injuries and Emergency Intensive Care Unit (EICU) of the Third Affiliated Hospital of Southern Medical University, China. Patients who meet the eligibility criteria and obtain informed consent will be assigned to the test group or control group in a 1:1 ratio based on the size of the random number allocated to them. Patients will be resuscitated with the drug according to the study arm, and only this drug will be used for resuscitation in the early fluid resuscitation (6 h) period. Approval has been obtained from the Institutional Ethics Committee (IEC) of the Chinese Ethics Committee of Registering Clinical Trials. This study complies with the Declaration of Helsinki and the relevant regulations for clinical research in China. This trial has been registered as ChiCTR2100045044.

The protocol is written in accordance with the Standard Protocol Items: Recommendations for Interventional Trials (SPIRIT) guidelines, shown in Additional file 2. Figure 1 (study scheme) shows an overview of the study process. Figure 2 shows the schedule of enrolment, interventions, and assessments.

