### Secondary endpoints

(A)The amount of drug use, the total amount of resuscitation fluid, and the use of vasoactive drugs was compared in each study arm.(B)The total number of deaths and mortality was compared. The Kaplan–Meier survival curve was drawn, and the 7-day mortality of patients in each study arm was compared.(C)The levels of inflammatory mediators (PLA2, TNF- α, IL-6, PCT, CRP) were compared in each study arm.(D)The recurrence rate of shock and the complications of survival cases (ARDS, AKI, TIC, MODS, etc.) were compared among the study arms.(E)Blood coagulation and platelet function (PT, APTT, TT, INR, ACT, Fib, VEM) were compared among different study arms and before and after treatment.(F)Body temperature and acidosis (T, PH, BE, Lac, PaCO_2_, HCO_3_^−^) was compared among different study arms and before and after treatment.(G)The mechanical ventilation time, EICU hospitalization time, and total hospitalization time of patients in each study arm was compared.

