#### Lactic acid clearance rate of 6 h

The lactic acid in the blood gas results is recorded before fluid resuscitation (0 h) and after resuscitation (0.5, 1, 1.5, 3, and 6 h). The lactic acid clearance rate at the above is calculated based on the time point change in the lactic acid.

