#### Sample size

The trial design of this study was a positive drug, parallel-group, and superiority verification. The primary endpoint is the duration of shock and lactic acid clearance rate during the early fluid resuscitation period (6 h). Both primary endpoints were required to be met simultaneously, and Bonferroni correction was used as appropriate. The alpha value = 0.025 (one-sided), power = 0.80 were set. The total sample size was finally determined to be 400 cases with 200 cases in each study arm.

The calculations were as follows:Lactic acid clearance rate: According to a study by Wang et al., the mean value of lactic acid clearance rate after 6 h of fluid resuscitation in the control group was 32% with a standard deviation of 10%, and the expected lactic acid clearance rate after 6 h of fluid resuscitation in the test group was 35% with an equal standard deviation for both study arms [42]. The calculated sample size was 176 cases for each study arm, and a total of 392 cases were required based on 10% of the loss to follow-up.Duration of shock: According to the pre-experimental study, the duration of shock in the control group was 3 h, and in the test group the duration of shock was 1.5 h, with a standard deviation of 4 h. Assuming equal standard deviation for both study arms, the sample size calculated for both study arms was 113 cases, and a total of 252 cases were required based on 10% of the loss to follow-up.

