#### Statistical analysis

This trial was performed using SPSS 26.0 for data analysis. A general linear model was used to correct for selection bias between the two study arms. Categorical data were described as percentages. The measurement data were tested for normality, approximately normal or normally distributed measures were expressed as mean ± standard deviation (x ® ± s), and non-normally distributed measures were expressed as median (quartiles). The chi-square test/ Fisher’s precision probability test was used for categorical data. Paired *t*-test/rank sum test/one-way repeated measures ANOVA/two-way repeated measures ANOVA was used for the measurement data. Kaplan–Meier survival curves were plotted for survival analysis of patients, and differences between the two study arms were compared using the log rank test. Multiple regression analyses were selected to analyze the interrelationships between the factors. The missing data were handled using the last observation carry forward (LOCF) method, and sensitivity analysis was performed using the multiple imputation method. *P* < 0.05 was statistically significant.

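### LOCF as the main missing-data method can bias the 6-hour lactate clearance comparison and costs power; it should not be the primary rule

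*Protocol article*

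**What the plan says.** The Statistical analysis section of the protocol article sets the rule for all missing data: "The missing data were handled using the last observation carry forward (LOCF) method, and sensitivity analysis was performed using the multiple imputation method". LOCF is therefore the main method, and multiple imputation only checks it.

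The rule reaches the co-primary endpoint, lactate clearance at 6 h. The section headed Lactic acid clearance rate of 6 h schedules one sample at 0 h and further samples at 0.5, 1, 1.5, 3 and 6 h. On the calculation it says: "The lactic acid clearance rate at the above is calculated based on the time point change in the lactic acid". So up to five earlier values, including the one at 0 h, are available to be carried to 6 h. The Sample size section adds that "Both primary endpoints were required to be met simultaneously, and Bonferroni correction was used as appropriate", so a distortion of the lactate result alone can decide the trial.

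Missing 6-h values are foreseeable. Sample size allows for 10% loss. Stopping criteria removes patients for transfusion, intervention or surgery within 1 h of admission, death within 1 h of the intervention, serious adverse events, withdrawal and incomplete observation, and partly at the physician's discretion. Blinding describes an open trial.

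**The concern.** LOCF gives the right 6-h value only if nothing changes after the last sample. Here change over the window is what is being measured. Clearance is expected to rise over the 6 h, so a value from 0.5, 1, 1.5 or 3 h will usually be lower than the value the patient would have reached. If sampling ends when a patient is stopped, that partial clearance is analysed as the final one. A patient who dies may be credited with the last living value.

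Two harms follow. With equal missingness, the mixture of finished and unfinished values widens the spread and slightly shrinks the difference. With unequal missingness, the arm with more missing values is penalised whatever the fluid does. Unequal missingness is plausible because the reasons for stopping relate to outcome, some rest on judgement, and staff know the arm. The planned effect is only 3 percentage points, so a shift of 1 or 2 points matters.

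**Working it through.** **Inputs from the Sample size section.** Clearance at 6 h is 32% (control) and 35% (test), with SD 10 in both arms; one-sided alpha is 0.025, power 0.80, loss 10%, and 200 patients per arm.

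**Assumptions not in the documents.** The share *m* of patients in an arm with no 6-h value; the fraction *f* of the 6-h clearance reached at the last value (central 0.5, range 0.25 to 0.75); SD 10 for the carried value; missingness random within each arm.

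**The plan's own figure.** *n* per arm = 2 × (1.960 + 0.842)² × 10² / 3² = 174.4, so 175 by the normal approximation and 176 with the t-test. 176 / 0.9 gives 196 per arm, 392 in total. The stated numbers reproduce, as an independent two-sample comparison of 6-h clearance.

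**LOCF as a mixture.** For an arm with true mean μ:
- mean = μ × [1 − *m*(1 − *f*)]
- variance = 100 + *m*(1 − *m*) × [(1 − *f*)μ]²
- standard error of the difference = √[(variance, control + variance, test) / 200]
- probability of rejecting = 1 − Φ(1.960 − difference / standard error)

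**Case 1: 10% missing in each arm, true difference 3.** With *f* = 0.5:
- means 32 × 0.95 = 30.40 and 35 × 0.95 = 33.25; difference 2.85
- variances 100 + 0.09 × 16² = 123.0 and 100 + 0.09 × 17.5² = 127.6; SD about 11.2
- standard error √(250.6 / 200) = 1.119; power 0.72

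Over *f* = 0.25 to 0.75 the difference is 2.77 to 2.93 and power 0.60 to 0.81. The 180 per arm with an observed 6-h value would give 0.81 on their own, so LOCF here does no better than leaving the missing values out, and usually worse.

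**Case 2: no true effect, 15% missing in control and 5% in test.** With *f* = 0.5:
- means 32 × 0.925 = 29.6 and 32 × 0.975 = 31.2; false difference 1.6
- variances 100 + 0.1275 × 256 = 132.6 and 100 + 0.0475 × 256 = 112.2
- standard error √(244.8 / 200) = 1.106; one-sided error 0.30 instead of 0.025

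Over the range of *f* the false difference is 0.8 to 2.4 and the error 0.12 to 0.50.

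**Case 3: milder imbalance, no true effect, 12% control and 8% test.** False difference 0.04 × 16 = 0.64; error 0.08 (0.05 to 0.12).

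**Case 4: reverse imbalance, 5% control and 15% test, true difference 3.** Means 32 × 0.975 = 31.20 and 35 × 0.925 = 32.375; difference about 1.2 (0.3 to 2.1); power about 0.18.

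A simulation of 5,000 trials, with *f* = 0.5 and a within-patient correlation of 0.6, agrees: differences of 2.86, 1.61 and 1.20 for cases 1, 2 and 4, with rejection rates of 0.72, 0.30 and 0.20.

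**The case against.** The strongest objection concerns size. The document gives neither the share of missing 6-h values, nor its split by arm, nor the lactate curve. The 10% is a general loss allowance, not a count of missing blood gases. An error near 0.30 needs a 10-point imbalance; milder splits give roughly 0.05 to 0.11, and the reverse imbalance works against the test fluid. This stands, so LOCF *can* bias the result, by an amount that cannot be fixed in advance. It does not defend LOCF as the main rule.

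It is also unclear whether deaths reach LOCF at all, because the Exclusion criteria list patients who die during the study. That is a reason to state how deaths are handled.

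Three stronger readings are tempting but unsupported.

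- *Paired tests or repeated-measures ANOVA are used to compare the arms.* The section says only that "Paired *t*-test/rank sum test/one-way repeated measures ANOVA/two-way repeated measures ANOVA was used for the measurement data"; it ties none of these to the arm contrast. Secondary endpoints plans comparisons both ways ("was compared among different study arms and before and after treatment"), which paired tests and one-way ANOVA fit. An arm-by-time ANOVA is valid for independent arms, a rank sum test can be, and a general linear model is also named ("A general linear model was used to correct for selection bias between the two study arms"). Even a paired test misapplied to independent arms would be unbiased, with power 0.799 against 0.801 at 176 per arm.
- *Repeated-measures ANOVA discards incomplete patients.* Under LOCF the later gaps are already filled for anyone with a baseline value.
- *Baseline adjustment would bring a large gain in power, to 0.87 to 0.94.* That needs baseline-to-6-h correlations of 0.7 to 0.3. Clearance of 32% with SD 10 implies a log-ratio SD of about 0.10 / 0.68 = 0.147. With equal log variances at both times, those correlations require a baseline log-lactate SD of only 0.147 / √[2(1 − r)], that is 0.19 to 0.12. This is narrow for an entry rule of lactate above 2 mmol/L with no upper limit. If the SD were 0.3 to 0.5 (an assumption), the variance would fall by only about 2 to 6%.

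Which listed method gives the primary estimate may be settled in an analysis plan that is not shown. LOCF as the main method is stated in the article itself.

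**Conclusion.** The concern holds for LOCF as the main missing-data method for 6-h lactate clearance. It is an explicit choice, poorly suited to an endpoint that moves through the window and to missingness linked to early stopping in an open trial. Confidence is high that the rule is unsuitable, and lower for the size and direction of the effect.

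Under the assumptions shown, equal 10% missingness costs about 9 points of power. Unequal missingness moves the difference by roughly 0.3 to 2.4 points under no true effect, against a planned 3. The upper end needs both a large imbalance and early last values. If missingness at 6 h is rare and balanced, the damage is small. Nothing here changes the stated sample size, and the list of tests is not itself an error on this point.

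**What to change.** Replace the missing-data sentence in Statistical analysis so that LOCF is no longer the main method.

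- **Primary analysis of 6-h lactate clearance:** a likelihood-based mixed model for repeated measures on the serial values already collected, with arm, time, arm by time and baseline lactate as a covariate, testing the arm contrast at 6 h. Alternatively, make multiple imputation primary. Keep clearance as the declared endpoint; a log-lactate analysis is optional.
- **Deaths before 6 h:** state how they enter the primary analysis, and add a sensitivity analysis that assigns them the worst value. Both primary options assume data missing at random, which death may not satisfy.
- **LOCF:** at most a sensitivity analysis.
- **Reporting:** give the number and timing of missing lactate values by arm.

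The cost is an amendment of wording and slightly more analysis work. The samples are already scheduled and no interim analysis is planned. Recruitment began in May 2021 and allocation is open, so the change should be dated and fixed before the database is locked.

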#### Interim analyses

No interim analysis will be performed.

#### Pharmacovigilance plan

An adverse event (AE) is defined as any adverse medical event that occurs to a patient, which does not necessarily have a causal relationship with the treatment. Therefore, an adverse event can be any discomfort or unconscious signs (including abnormal laboratory results), symptoms, or disease after using the drug, whether or not it is considered drug-related. Such incidents can occur when used by the drug instructions or due to accidental or intentional overuse, drug abuse, or drug withdrawal. Any pre-existing condition or deterioration of the disease is also considered to be adverse. If it meets any of the following criteria, it will be considered a serious adverse event (SAE): the subjects died, endanger one’s life, extended hospital stay / ICU time, persistent or apparent disability/loss of function, an important medical event that requires medication or surgery to avoid serious consequences. In the event of a serious adverse event, whether or not the incident is related to the research drug or reference substance (if applicable), the doctor should notify the Research Supervision team within 24 h of the incident. The specimen management system for patients with adverse events will actively treat the patients and terminate the trial in the event of adverse events, and the remaining drugs will be uniformly recovered and centrally destroyed. The patient’s blood, body fluids, secretions, and other test-related specimens will be destroyed and recorded under the supervision of the main person in charge and the inspectorate.

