**Methods:**

/design.

This single-center, prospective, randomized controlled trial will focus on the efficacy and safety of BRS in early THS resuscitation. A total of 400 adults THS patients will be enrolled in this study. In addition to providing standard care, enrolled patients will be randomized in a 1:1 ratio to receive resuscitation with BRS (test group) or sodium lactate Ringer’s solution (control group) until successful resuscitation from THS. Lactate clearance at different time points (0.5, 1, 1.5, 3, and 6 h) and shock duration after drug administration will be compared between the two groups as primary end points. Secondary end points will compare coagulation function, temperature, acidosis, inflammatory mediator levels, recurrence of shock, complications, medication use, and 7-day mortality between the two groups. Patients will be followed up until discharge or 7 days after discharge.

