### Objectives

By comparing the differences in duration of shock and the lactic acid clearance rate at each time point when early fluid resuscitation was performed in the test group and control group. To identify whether early fluid resuscitation using BRS can reduce the complication rate and improve 7-day survival in patients with THS.

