### Eligibility criteria

#### Inclusion criteria

Patients with THS [39, 40] (Table 1 shows the diagnostic criteria for THS)Age ≥ 18 years

**Table 1 Tab1:** The diagnostic criteria for THS. Patients who at the same time meet Clinical history, Vital signs^1^, and any three of Vital signs^2^ will be diagnosed as THS

Clinical history	Vital signs^1^	Vital signs^2^
There are traumas that cause hemorrhage (such as road traffic injuries)	(1) Systolic blood pressure (SBP) < 80 mmHg, or mean arterial pressure < 65 mmHg, or a decrease of ≥ 40 mmHg from baseline. (2) Lactate level > 2 mmol/L.	(1) Consciousness changes, includes unresponsiveness, disorientation, and confusion. (2) The skin is wet and cold with vasoconstriction and cyanosis floridis, capillary filling time > 2 s. (3) Urine output < 0.5 ml/kg/h. (4) Pulse rate > 100 beats/min or untouchable, shock index > 1.0.

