#### Complications

Complications (ARDS, AKI, TIC, MODS, etc.) that occurred during the entire study process will be recorded and confirmed through corresponding diagnostic methods.

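### The adverse-event definition contradicts itself by counting pre-existing conditions; read literally, every patient has an adverse event at entry and a crude any-event comparison is uninformative

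*Protocol article*

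**What the plan says.** All references are to the protocol article.

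- **Pharmacovigilance plan, opening.** "An adverse event (AE) is defined as any adverse medical event that occurs to a patient", with no causal link required. The text goes on to cover signs, "including abnormal laboratory results), symptoms, or disease after using the drug, whether or not it is considered drug-related".
- **Pharmacovigilance plan, later sentence.** "Any pre-existing condition or deterioration of the disease is also considered to be adverse".
- **Inclusion criteria, Table 1.** Every patient must have a bleeding injury, low or fallen blood pressure, "Lactate level > 2 mmol/L", and at least three of four further signs of shock.
- **Abstract, Methods.** The trial "will focus on the efficacy and safety of BRS in early THS resuscitation".
- **Objectives.** "To identify whether early fluid resuscitation using BRS can reduce the complication rate and improve 7-day survival in patients with THS".
- **Complications.** "Complications (ARDS, AKI, TIC, MODS, etc.) that occurred during the entire study process will be recorded", with diagnostic confirmation. No reference to status at 0 h is given.
- **Primary endpoint and Secondary endpoints.** Neither list contains an overall adverse-event rate.

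**The concern.** An adverse-event count informs on a treatment only if it separates what happened after the treatment from what the patient arrived with. The later sentence removes that separation, and it does so in a population where every patient arrives with a grave condition. Anyone who applied it as written would report an any-event proportion that cannot differ between arms, and equality might be taken as reassurance about the test fluid.

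There is also a knock-on. The serious category in the same section includes danger to life and important events needing medication or surgery. Presenting hemorrhagic shock, once classed as an adverse event, plausibly meets these criteria. The Stopping criteria and Termination study conditions attach consequences to serious events, and the Pharmacovigilance plan attaches trial termination to adverse events.

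**Working it through.** **Planning figures.** The protocol gives no adverse-event rate to reproduce. Its sample sizes (176 per arm for lactate clearance, 113 per arm for shock duration, 400 enrolled) do not involve the adverse-event definition and are unaffected.

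**Step 1: the two statements side by side.** The opening of the definition requires occurrence, and its list of signs, symptoms and laboratory results is tied to the time after drug use. The later sentence joins a pre-existing condition and deterioration of the disease with an *or*, so either alone suffices. A condition present before the drug is outside the first statement and inside the second.

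**Step 2: apply the literal rule to the entry criteria.** Traumatic hemorrhagic shock is required at entry, so every patient has at least one qualifying pre-existing condition.

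- Any-event proportion, each arm: 200/200 = 100%.
- Both arms: 400/400.
- Risk difference: 1.00 − 1.00 = 0, for any true effect of the fluid.

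**Step 3: would deleting the sentence be enough?** The laboratory clause is limited to results after the drug, so lactate measured at 0 h falls outside it. The clause does not, however, require a change from 0 h. The Sample size section assumes mean 6 h clearance of 32% (control) and 35% (test). Assuming clearance c means a fractional fall from the 0 h value, lactate at 6 h is L0 × (1 − c), which exceeds 2 mmol/L when L0 > 2/(1 − c):

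- c = 0.32: L0 > 2/0.68 = 2.94 mmol/L.
- c = 0.35: L0 > 2/0.65 = 3.08 mmol/L.

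A patient with average clearance who enters above about 3 mmol/L would still be above 2 mmol/L at 6 h, although improving. Without a 0 h reference, that result could be counted as an event after drug use. The laboratory clause therefore needs the reference too.

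**Step 4: complications, as a conditional illustration.** Suppose a share p in both arms already has the condition at 0 h and is counted as a case. With risks r1 and r0 among the others:

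observed difference = [p + (1 − p)r1] − [p + (1 − p)r0] = (1 − p)(r1 − r0).

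The protocol gives no value for p. Assuming p = 0.10 to 0.40, the observed difference is 0.90 to 0.60 of the difference among patients free of the condition at 0 h. This applies only if cases present at 0 h are counted, which the Complications section does not say.

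**The case against.** The strongest reply is that one clumsy sentence is being read against its context. The definition opens with an event that occurs and continues with the period after drug use, so the sentence may have been meant as deterioration of a pre-existing condition. That is a plausible intention. But the sentence as printed names the condition itself, and a stated rule that says the wrong thing is not a detail left to a fuller document.

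A reader might infer that the trial cannot answer its safety question at all. The documents do not support that. Overall adverse-event incidence is not a listed endpoint, and the stated objective concerns complications and 7-day survival. The Secondary endpoints compare 7-day mortality, shock recurrence, complications, and coagulation and acid–base values before and after treatment, with 0 h samples. None of these uses the adverse-event definition. Even under the literal reading, only the crude any-event proportion is certain to saturate; event types and severity could still differ between arms.

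A reader might also infer that abnormal laboratory results at entry count under the laboratory clause. They do not, because that clause is limited to the time after drug use; they could enter only through the pre-existing-condition sentence.

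On complications, the objection largely stands. Occurrence during the study can mean new onset, and diagnostic confirmation is required. Low urine output is one of four signs of which any three suffice, and it is not in itself a diagnosis of AKI. Cases present at 0 h should balance on average under randomization, so counting them would attenuate a difference, not bias the comparison towards one arm. What remains is an ambiguity, clearest for traumatic coagulopathy.

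**Conclusion.** The adverse-event definition contradicts itself on pre-existing conditions and should be corrected. Taken literally with Table 1, it gives 100% in each arm and a risk difference of 0, so a crude any-event comparison would say nothing about either fluid. This size rests on the literal reading; it is not a figure the protocol reports. The defect is limited to summaries and rules that use this definition, and the other safety-relevant comparisons stand apart from it. The complications issue is secondary: an unstated 0 h rule, with attenuation to 60–90% only under the assumed prevalence of 10–40% and only if prevalent cases are counted. The link to the serious-event rules is a consistency problem between sections that follows from the same sentence.

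**What to change.** - **Pharmacovigilance plan:** reword so that conditions and abnormal results present at 0 h are recorded as baseline, and only events that are new, or worse than at 0 h, after the first study fluid count as adverse events. Apply this to laboratory results as well.
- **Complications:** for conditions that can already exist at 0 h, such as traumatic coagulopathy, state that only cases absent at 0 h count, using the 0 h samples already scheduled.
- **Stopping criteria, Termination study conditions and Pharmacovigilance plan:** reconcile these so that it is clear whether the presenting shock can fall under the serious-event wording. Which stopping rule should apply is for the sponsor and investigators to settle.

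The cost is wording in these sections and a derived variable for change from 0 h, with no additional sampling. Reported event rates will be lower. The Trial status section expected recruitment to run to June 2024; if the analysis has not been done, the revised rule can be applied to all patients from their 0 h data.

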## Abstract

**Background:**

Traumatic hemorrhagic shock (THS) is the main cause of death in trauma patients with high mortality. Rapid control of the source of bleeding and early resuscitation are crucial to clinical treatment. Guidelines recommend isotonic crystal resuscitation when blood products are not immediately available. However, the selection of isotonic crystals has been controversial. Sodium bicarbonate Ringer solutions (BRS), containing sodium bicarbonate, electrolyte levels, and osmotic pressures closer to plasma, are ideal. Therefore, in this study, we will focus on the effects of BRS on the first 6 h of resuscitation, complications, and 7-day survival in patients with THS.

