## Discussion

THS is a common serious complication of severe trauma. Without aggressive and effective treatment, it can lead to a series of serious consequences (e.g., uncorrected acidosis, hypothermia, TIC) and extremely high mortality, requiring continuous and comprehensive treatment. To improve the success rate of THS surgical rescue, shorten the time of shock, improve the prognosis, and reduce the economic burden of patients are urgent clinical problems to be solved. What kind of fluid to choose in early resuscitation and what kind of resuscitation method to use can reduce mortality and complications are the hot spots of current attention. Moreover, there is a lack of systematic and detailed studies on the effect of different infusion on the efficacy and safety of resuscitation in THS patients, and there is no unified standard to guide clinical treatment.

Since the composition of BRS is more similar to plasma, BRS has shown its advantages over other liquids in the current study. BRS is shown to improve metabolic acidosis, maintain acid–base balance, prevent arrhythmias, and supplement circulating blood volume in the perioperative period [36–38]. G Tom Shires’ and Laura Boomer’s studies have shown that using BRS could significantly reduce apoptosis levels in lung and liver tissue and inhibit pro-inflammatory responses [32, 33]. Shinji Oikawa’s study showed that BRS has the positive capability to maintain PLT function [34]. A small clinical trial with a sample size of 50 showed that resuscitation with BRS improved coagulation function, lactate levels, pH, and hemorheological indices in patients [35].

However, these trials are mainly in vitro or perioperative studies, and there is a lack of large-scale credible clinical studies to demonstrate the use of BRS in early fluid resuscitation in THS. The only study in THS patients was small in size, lacked continuous observation of the entire resuscitation process, lacked subgroup analysis of different injury types, and had simple observation parameters. Therefore, a large clinical trial with sufficient sample size is needed, not only to continuously observe the entire resuscitation process and prognosis, but also to perform subgroup analysis of patients with different injuries, and to have more comprehensive observation parameters to confirm the benefits and limitations of BRS in the early resuscitation of THS patients.

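### As written, one serious adverse event, including any death, terminates the trial, which contradicts the planned mortality comparison and the enrolment of 400 patients

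*Protocol article*

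**What the plan says.** Four parts of the protocol article bear on this.

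- **Termination study conditions.** The first item calls for the trial to be terminated when an SAE occurs in it. It sets no number of events and no relatedness condition. The other items concern a major error or serious deviation in the scheme, lack of effect against control, and a request involving the sponsor.
- **Pharmacovigilance plan.** The seriousness criteria begin "it will be considered a serious adverse event (SAE): the subjects died" and go on to danger to life, a longer hospital or ICU stay, disability and important medical events. An adverse event counts "whether or not it is considered drug-related", and worsening of the underlying condition is included: "Any pre-existing condition or deterioration of the disease is also considered to be adverse". A later sentence, on patients with adverse events, says that staff will treat them and "terminate the trial in the event of adverse events, and the remaining drugs will be uniformly recovered and centrally destroyed".
- **Stopping criteria.** A separate list, mostly about individual patients, already includes those who have an SAE.
- **Secondary endpoints, Statistical analysis and Sample size.** Deaths are counted, "the 7-day mortality of patients in each study arm was compared", and complications such as ARDS, AKI and MODS are compared. Survival is analysed by Kaplan–Meier curves and the log-rank test. The target is 400 patients, 200 per arm.

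No section exempts deaths, or other events that are trial endpoints, from the termination item.

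**The concern.** A death is an SAE by definition, and an SAE closes the trial by rule. A trial that closes at its first death cannot compare mortality between arms, and in a condition that the abstract describes with the words "Traumatic hemorrhagic shock (THS) is the main cause of death in trauma patients with high mortality" it is unlikely to reach its sample size. The two primary endpoints would then fall short of the numbers they were powered on, and the mortality and complication comparisons could not be made. The text does not say which instruction gives way, so anyone following the protocol has to disregard either the termination item or the endpoints.

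**Working it through.** **1. The plan's own figure.** Sample size gives one-sided alpha 0.025, power 0.80, lactate clearance 32% against 35% with SD 10%, shock duration 3 h against 1.5 h with SD 4 h, and 10% loss. With n per arm = 2(1.960 + 0.842)²(SD/difference)²:

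- Lactate clearance: 2 × 7.849 × (10/3)² = 174.4, so 175. The noncentral t calculation gives 176, as stated.
- Shock duration: 2 × 7.849 × (4/1.5)² = 111.6, so 112. The noncentral t calculation gives 113, as stated.
- Loss: 176/0.9 = 195.6, so 196 per arm and 392 in total; 113/0.9 = 125.6, so 126 per arm and 252 in total. The larger total is rounded up to 400.

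The target of 400 reproduces and is not in question.

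**2. Is the item a trial-level rule?** It stands under its own heading, apart from Stopping criteria. The items beside it (scheme error, no effect against control, sponsor request) make sense only for the whole trial. Read as a per-patient rule, it would repeat what Stopping criteria already says about SAEs. The sentence in the Pharmacovigilance plan is less clear and could mean one patient's participation.

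**3. Chance of reaching 400 under the literal rule.** The documents give no death or SAE rate, so the per-patient risk p is an assumption and is shown as a range. With independent patients and a common p:

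- P(no event in 400) = (1 − p)^400
- expected number of patients up to the first event = 1/p
- median patient number of the first event = ln 0.5 / ln(1 − p), rounded up
- expected events in a full trial = 400p

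| Assumed p | P(no event in 400) | Mean patients to first event | Median | Events expected in 400 |
|---|---|---|---|---|
| 0.25% | 36.7% | 400 | 277 | 1 |
| 0.5% | 13.5% | 200 | 139 | 2 |
| 1% | 1.8% | 100 | 69 | 4 |
| 2% | 0.03% | 50 | 35 | 8 |
| 5% | 1.2e-9 | 20 | 14 | 20 |

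Solving (1 − p)^400 = 0.5 gives p = 0.17%. Solving for 0.05 gives p = 0.75%. Above a risk of about three quarters of one percent, the trial has less than a 5% chance of completing.

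**4. The mortality comparison.** This part needs no assumed rate. If the trial closes at its first death, with equal numbers at risk in the two arms, the log-rank statistic has observed minus expected = ±0.5 and variance 0.5 × 0.5 = 0.25. Chi-square is 0.5²/0.25 = 1, two-sided P about 0.32, whichever arm the death falls in. A few more deaths among patients already enrolled would not change the picture.

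**The case against.** The best reply is that the article uses trial and study loosely. The list under Stopping criteria includes termination of the study by the investigator in a sense that there means one subject, and the Pharmacovigilance sentence on terminating the trial sits among instructions about affected patients. The SAE item could be the same slip. This carries weight for the Pharmacovigilance sentence. It carries little for Termination study conditions, for the reasons in step 2 of the working.

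A second reply is practical. Trial status says recruitment began on 1 May 2021 and was expected to end in June 2024, and version 5.0 is dated 6 September 2022, some 16 months in. That points away from literal use of the rule. It does not amend the text.

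A third is that this is a condensed article and that thresholds and review procedures belong in the full protocol. That is right, and their absence is not the point here. The point is that the rule the article does state conflicts with the endpoints and sample size it also states.

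Several stronger readings are tempting and are not supported:

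- *The trial would stop within its first few patients.* This depends on a risk the documents do not give. At 1% the first event is expected after about 100 patients. The Discussion's phrase "extremely high mortality" refers to shock without aggressive and effective treatment, so it supplies no rate for treated patients.
- *Nearly every patient has an SAE by definition.* Only an extended stay counts, not every EICU or hospital stay that is compared as an endpoint, and damage control surgery is listed as standard care. Deaths and serious complications are the sound part of the overlap.
- *Unblinded investigators could close the trial at will.* The trial is open, but the SAE item does not say who decides, and SAEs are reported to a Research Supervision team within 24 h. This harm is inferred, not documented.

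**Conclusion.** The contradiction stands and should be corrected. As written, the first item of Termination study conditions cannot be followed together with the between-arm comparison of deaths and 7-day mortality, whatever the event rate. Its conflict with enrolling 400 is a matter of probability: about a 37% chance of completing at an assumed risk of 0.25% per patient, 1.8% at 1%, 0.03% at 2% and 1e-9 at 5%. These figures assume independent patients and a common risk. Counting non-fatal SAEs as well as deaths raises p and lowers the chance. The finding concerns the wording. It does not show that the rule has been applied, that any closing decision was improper, or that the sample size is wrong.

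**What to change.** Amend the first item of Termination study conditions and the sentence on terminating the trial in the Pharmacovigilance plan, so that both agree with Stopping criteria, Secondary endpoints, Sample size and Statistical analysis. The amended text should make two things clear:

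- whether each rule ends one patient's participation or the whole trial;
- how SAEs that are themselves endpoints, such as deaths and complications, are handled so that the planned mortality comparison remains possible.

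The condition for closing the trial is for the sponsor and the ethics committee to set, and none is proposed here. If SAEs are to be reviewed by arm during the trial, the text should call this a safety review and reconcile it with Interim analyses, which plans none. Deaths are SAEs, so a by-arm review is also a look at a secondary endpoint.

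The cost is amendment wording, plus whatever safety review the sponsor chooses. No patients, visits or tests are added.
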